**Figure 5 figure5:**
[figure not shown]
The Axivity AX3 accelerometer as the measurement device.

### Additional Measurements for Exploratory Analyses

Besides primary and secondary outcomes and demographic and clinical data collected as part of the usual care, we will also collect app usage data and additional self-report measures for exploratory analyses. App usage data can provide preliminary insights into the role of specific features of the app in its overall effectiveness by correlating outcome variables with usage metrics, including login frequency, frequency of monitoring one’s step data (Figure 4C), coaching message frequency, and coaching message content.

Additional self-report measures are used to assess patients’ baseline PA levels before their cardiac events and to examine the dynamics of their psychological states over the weeks between the intervention and the control group. A complete list of the self-report measures in English can be found in Multimedia Appendix 2. All questions will be translated into Dutch for the trial.

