#### The Mobile-Based Coaching App

Patients in the intervention group will also be monitored and coached by nurse practitioners through an e-coaching app called Heart Angel, which is a customized version of the commercial Virtuagym platform [38]. We decided to use this particular app because (1) the platform meets our needs for e-coaching and is free; (2) a customized version tailored to the context of CR was made available; and (3) the platform works seamlessly with the Neo Health One self-tracking device. The nurse practitioners work at the same cardiac surgery department at CZE and are known by the patients during their stays at the hospital, and they receive a 1-day training to use the platform provided by the researchers. The patients will use a mobile version of the Heart Angel app, while the nurse practitioners will use an associated web platform for coaching.

The Heart Angel app serves the following functions. First, the daily walking exercise program is saved and shown in the app, so the patients can always open it to review their goals and plans (Figure 4B). Second, data from the self-tracking device are transmitted to the app, so both patients and their coaches (the nurse practitioners) can monitor their PA performance using the app (Figure 4C). Third, the mobile app sends daily notifications in the morning to remind the patients of their planned daily step goals, and whenever a goal is reached, they receive achievement badges from the app. Fourth, when there is a need to contact their coach, the patients can send messages through the mobile app (Figure 4D). Conversely, the nurse practitioners are asked to closely monitor their patients’ compliance and performance, and to coach them whenever needed through the app, for example, to check for problems if a patient is not exercising sufficiently according to the plan, or to compliment a patient who is doing well. As the above functionalities are prototypical for e-coaching platforms in general, our RCT is meant to be an evaluation of the general functionalities of e-coaching rather than the Heart Angel app per se.

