One apparent limitation of the study is that the 2 home-based CR conditions are not directly compared with the usual care. Although ideally adding such a baseline condition is useful, given practical constrains (eg, time, financial resources) our design can be justified. Both previously published research [9] and expert opinions from local physicians suggest that under the current practice, patients are clearly not supported enough and they do not exercise enough during the gap period. Thus, compared with this *straw man* condition, the condition with the low-tech exercise program is a more meaningful baseline for evaluating the technologies, because it requires minimum effort to improve the usual care. Another limitation is that our experimental design does not allow us to disentangle the beneficial effects of self-tracking and e-coaching. For example, it might be that self-tracking is the main active component of the intervention, so the costs associated with human coaching can be saved. While future research is needed to accurately separate the effects, the planned exploratory analyses on app usage data may provide preliminary answers. A third limitation relates to potential reactivity to the measurement device in the control group. Although the Axivity AX3 device does not support self-monitoring, merely wearing the device may increase patients’ awareness of their PA levels and motivate to perform more activities [56-59]. This limitation does not invalidate the testing of the differences between the trial conditions, but caution should be exercised when generalizing the results of the control group to the low-tech solution in practice. Despite the limitations, our study should provide valuable data for bridging the discharge–rehabilitation gap in the current CR practice and more generally contribute to the growing literature on enhancing traditional center-based CR with digital technologies [6,21].

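### Correlating steps with coaching message frequency cannot show what coaching does, because coaches message patients in response to their activity

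*Protocol article*

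**What the plan says.** Under Additional Measurements for Exploratory Analyses, the protocol article expects records of app use to yield "preliminary insights into the role of specific features of the app in its overall effectiveness by correlating outcome variables with usage metrics". The metrics are login frequency, how often patients look at their step data, and "coaching message frequency, and coaching message content". No time lag, adjustment or unit of analysis is given.

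Under The Mobile-Based Coaching App, nurse practitioners can see patients' activity data and are asked to follow compliance and performance closely. They coach when the need arises, and the two reasons named are "to check for problems if a patient is not exercising sufficiently according to the plan, or to compliment a patient who is doing well".

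Under Primary and Secondary Outcomes, the main outcome is average daily steps over the 3 weeks, which is the period in which the messages are sent.

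The Discussion concedes that the design cannot separate self-tracking from e-coaching. It gives as an example that "it might be that self-tracking is the main active component of the intervention, so the costs associated with human coaching can be saved", and then says: "While future research is needed to accurately separate the effects, the planned exploratory analyses on app usage data may provide preliminary answers".

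**The concern.** The planned correlation has a causal purpose: to learn which feature of the app contributes to its effect. For coaching messages, the exposure is set partly by the outcome. A coach who sees too little walking writes to the patient, and a coach who sees good progress also writes. Coaches see wristband steps and the outcome comes from the hip accelerometer, but both record the same walking. A patient's message count over 3 weeks therefore depends on that patient's average steps over those weeks, whatever the messages do.

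If contact goes mainly to low walkers, useful coaching can appear to go with fewer steps. If compliments dominate, coaching without effect can appear helpful. At stake is the interpretation of the one analysis that the Discussion offers on the self-tracking versus coaching question. More patients would not cure the problem, because it is bias and not imprecision.

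Login and step-viewing frequency are not driven by the coaches' instruction. Their weakness is different: motivated patients may both open the app more and walk more.

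**Working it through.** **The plan's own figure.** No figure is stated for the usage analysis. The sample size supplies the 50 intervention patients and the scale of the steps. Inputs from Sample Size Calculation: difference 2000, SD 3000, power 90%, alpha .05 (two-sided fits; one-sided would give 39 per arm).

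n per arm = 2 × (1.960 + 1.282)² × (3000/2000)² = 2 × 10.51 × 2.25 = 47.3, so 48.

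Exact t-test power at 50 per arm is 0.91. The stated 50 per group is reproduced.

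**Simulation A.** 50 intervention patients, 21 days, 400 runs per setting. Assumptions, none of them in the documents: patient means normal with mean 5000 and SD 2700; day-to-day SD 2000; a message on 50% of trigger days and 15% of other days; each message raises the next day's steps by a fixed amount. The statistic is Pearson's r between a patient's message count and mean steps.

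| Who triggers contact | True effect per message | Mean r |
|---|---|---|
| Days under 4000 steps | 0 / 300 / 500 / 1000 | -0.74 / -0.73 / -0.72 / -0.70 |
| Days under 4000, 30% vs 15% | 500 | -0.44 |
| Days under 4000, 20% vs 15% | 500 | -0.17 |
| Low days, goals half tailored to the patient | 0 or 500 | about -0.6 |
| Low days relative to the patient's own level | 500 | -0.03 (95% range -0.34 to 0.26) |
| Days under 4000 and over 6000 alike | 500 | +0.09 (95% range -0.17 to 0.35) |
| High walkers | 0 or 500 | about +0.75 |

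In the first row, going from no effect to 1000 steps per message moves r by only 0.04 (-0.74 to -0.70). Changing who is contacted moves it by about 1.5 (-0.73 to +0.75).

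**Simulation B, with a larger and longer effect.** Mean 6000, between-patient SD 2970, day SD 2000; steps are raised by 2000 per day in the 3 days after a message. Low and high mean below and above 6000 steps where one side is targeted, and below 4000 and above 8000 where both are. The rate on other days is 0.15.

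| Message probability | Mean r, no effect | Mean r, effect 2000 |
|---|---|---|
| Unrelated to steps | -0.01 | +0.08 |
| Low 0.60 | -0.82 | -0.77 |
| Low 0.30 | -0.48 | -0.38 |
| Low 0.60, high 0.30 | -0.57 | -0.28 |
| Both 0.60 | +0.02 | +0.46 |
| Low 0.30, high 0.60 | +0.61 | +0.75 |
| High 0.60 | +0.82 | +0.80 |

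A large sustained effect does move r when both extremes are contacted. The value still cannot be interpreted without knowing the trigger: +0.46 arises here from a strong effect with equal contact, while +0.61 arises from no effect with more compliments than corrections.

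**Alternative model.** On Simulation A data, a patient-centred model of steps on day t+1 on messages on day t, adjusted for steps on day t, gave estimates of 12, 267, 461 and 924 for true effects of 0, 300, 500 and 1000 (SD about 150). It also recovered the next-day effect under the other contact patterns. If a 300-step effect instead carried over at 0.9 per day, the model returned about 219, although the accumulated effect per message is far larger. It measures short-term response only.

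**The case against.** Much of the caution is already in the text. The analysis is labelled exploratory, its results are called preliminary, and the Discussion says that the components cannot be separated by this design and that future research is needed. The article fixes neither the level nor the timing of the correlation, and Statistical Analysis already plans day-level multilevel models for steps. Message content is collected and could separate corrective from complimentary contact.

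This lowers the weight of the point but does not remove it. The article names a method and a causal purpose. It does not say that contact depends on steps, and it describes no use of message content or timing to deal with that.

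Three stronger readings are tempting and are not supported.

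- A reader might infer that r will be strongly negative, so that coaching will look harmful. That needs a fixed step threshold and contact mainly with low walkers. The coaching section judges sufficiency against the plan, The Daily Exercise Program sets durations individually within weekly ranges, and compliments are named in the same sentence as corrections.
- A reader might infer that the trial could end by recommending that coaching be dropped. The remark on saved costs is only an example of a possibility, with no decision rule behind it. The case for implementation rests on the randomised comparison.
- A reader might extend the reverse causation to all usage metrics. The coaches' instruction drives only the messages that coaches send; logins, step views and patients' own messages are a separate matter.

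**Conclusion.** The point holds in limited form. A correlation between coaching message frequency and average steps over the same 3 weeks mainly reflects whom the coaches chose to contact. It cannot indicate whether coaching or self-tracking is the active component. Under the assumed settings, r runs from about -0.7 through 0 to about +0.7. When contact is one-sided, it hardly depends on the true effect.

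The size rests on assumptions that the documents do not supply: trigger rates, thresholds, how far goals are tailored, and how long an effect lasts. The mechanism itself needs only the coaches' instruction and the shared 3-week window, and both are stated.

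Severity is minor to moderate. The analysis is exploratory, the authors already concede that the effects cannot be disentangled, and neither the primary nor the secondary randomised comparisons are affected.

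**What to change.** 1. For messages sent by coaches, replace the overall correlation with an exploratory day-level model within patients: steps on later days on messages on day t, adjusted for steps on day t and study day, with messages centred on the patient's mean. This extends the multilevel models already planned.
2. Code messages by sender and, using the content already to be collected, as corrective or complimentary.
3. State that the model captures short-term effects only and that time-varying confounding may remain, for example a bad day noticed by both patient and coach.
4. Describe associations with login and step-viewing frequency as open to confounding by motivation.
5. In the Discussion, say that usage correlations cannot attribute the effect to coaching or to self-tracking.

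The cost is some extra analysis and message coding. Dated message and usage logs are needed. The article does not say that the platform holds them. If it does, they must be exported and linked to daily steps before the Heart Angel server data are deleted, since Data Management and Ethics foresees archiving only anonymous, aggregated data. If dated logs are not available, item 5 becomes the essential change. No new patients or measurements are required.

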#### Physical Activity Levels Before Cardiac Events

Patients’ regular PA levels before their cardiac events will be measured using the validated International Physical Activity Questionnaire [46], available in Dutch.

#### Trait Self-Control

Trait self-control has been shown to relate positively to a variety of health outcomes [47,48] and to people’s abilities to form healthy lifestyle habits [49]. However, the role of self-control in CR following cardiac intervention has not been examined. We will use the 10-item Brief Trait Self-Control Scale [50].

#### Attitude Toward the Daily Walking Exercise

Attitude refers to the subjective evaluation of a behavior object as positive or negative [51], and it is one of the most studied and important determinants of behavior change [52]. We will explore how patients’ attitude toward PA changes over time and whether self-tracking and mobile-based coaching lead to more positive attitude. Attitude is measured using seven 7-point semantic differential scales, for example, *good*–*bad*, *beneficial*–*harmful*, *pleasant*–*unpleasant*.

#### Habit Strength of the Daily Walking Exercise

As a patient repeats the daily walking exercise in a stable daily environment, the behavior will potentially become habitual and more likely to be maintained outside the context of the study [36]. We are interested in the dynamics of this habit formation [53] and how the intervention and control groups would differ in this regard. The validated 4-item Self-Report Behavioral Automaticity Index will be used [54].

### Randomization and Blinding

Patients will be allocated to the intervention or control group through a computerized randomization procedure during the introduction meeting. Specifically, the procedure takes place after the introduction of the general study information and the daily walking exercise program, and before the tutorials about how to use the (condition-dependent) technologies. The timing of the randomization is designed to blind the experimenter (a nurse practitioner) to treatment allocation until the daily walking exercise program is fully introduced, in order to minimize potential biases in guiding and motivating the patients. As with most electronic health (eHealth) trials, patients in our trial are not blinded to their conditions. Assessors of the bicycle ergometer test will be blinded to the research purposes as well as treatment allocation.

### Patient Timeline

Patient timeline in this RCT is illustrated in Figure 6. During the preoperative screening in the outpatient clinic, patients are informed about the study and are given 1-2 weeks to make their participation decisions. If they agree to participate, a consent form is signed a few days before the surgery. After the surgery and the 3-5-day monitoring at the hospital, an introduction meeting with a nurse practitioner is held at discharge. In this meeting, the study goals and procedure are introduced first, and then the daily walking exercise program is explained and details are planned together with the patients. After the randomized group allocation, according to the assigned group, patients are handed the devices and are guided through the installation, registration, and use of the devices and the mobile app. After returning home, patients are expected to follow the exercise program at home for 3 weeks, before they are referred to the conventional CR program. Right after discharge and at the end of each study week, a questionnaire is sent to the patients by email to measure the variables of interest discussed above. After the 3-week trial, a bicycle ergometer test is scheduled to take place at the hospital within 1 week, where patients also return the devices. A final questionnaire is sent 1 week after the study to measure the same set of variables to explore the prolonged effects of the exercise program on patients’ psychological states. Eight patients from the intervention group will be randomly selected for an additional interview about their experience with the devices and the mobile app.

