**Methods:**

Based on a power analysis, we will recruit 100 cardiac patients and assign them evenly to the 2 parallel groups. Eligible patients are those who are scheduled in the postanesthesia care unit, know the Dutch language, have basic literacy of using smartphones, and are without medical conditions that may increase risks associated with PA. In a face-to-face meeting with a nurse practitioner, all patients are prescribed a 3-week exercise program at home (2 walking exercises per day with increasing duration), based on national and international guidelines and tailored to their physical conditions after cardiac intervention. Their physical activities (daily steps) will be measured by the Axivity AX3 accelerometer worn at hip position. Patients in the treatment group will also be supported by a Neo Health One self-tracking device and a mobile platform called Heart Angel, through which they are monitored and coached by their nurses. After the study, all patients will perform a bicycle ergometer test and return the devices within 1 week. In addition, 5 questionnaires will be sent to the patients by emails to assess their self-efficacy toward PA and other psychological states for exploratory analyses (at discharge, at the end of each monitoring week, and 1 week after the study). To minimize bias, the randomization procedure will be performed after introducing the exercise program, so the nurse practitioners are blind to the experimental conditions until that point.

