## Methods

### Design

The study (registered at Netherlands Trial Register NL8040) will have a parallel-group randomized experimental design with an allocation ratio of 1:1. Participants will be randomized to the intervention or the control group during the introduction meeting at the date of discharge (Figure 1). Variables regarding participants’ psychological states (eg, self-efficacy toward PA) will be measured repeatedly over the weeks during the experiment (see the “Outcomes” section for details). The protocol conforms to the SPIRIT 2013 statement [30] and is described according to the CONSORT-EHEALTH checklist [31] (Multimedia Appendix 1).

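### All five questionnaires follow randomisation and device hand-over, so the first self-efficacy and attitude scores and the recalled pre-event activity are not clean pre-randomisation measures

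*Protocol article*

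**What the plan says.** The order of events is explicit in the protocol article.

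- **Design:** "Participants will be randomized to the intervention or the control group during the introduction meeting at the date of discharge".
- **Randomization and Blinding:** within that meeting, "the procedure takes place after the introduction of the general study information and the daily walking exercise program, and before the tutorials" on the technologies. The same section states that "patients in our trial are not blinded to their conditions".
- **Patient Timeline:** "After the randomized group allocation, according to the assigned group, patients are handed the devices", and they are guided through installation and use. Then: "Right after discharge and at the end of each study week, a questionnaire is sent to the patients by email".
- **Abstract, Methods:** the five questionnaires are sent "at discharge, at the end of each monitoring week, and 1 week after the study". None is placed before the operation or before allocation.
- **Additional Measurements for Exploratory Analyses:** the extra self-report measures are meant to capture "baseline PA levels before their cardiac events and to examine the dynamics of their psychological states" over the weeks, compared between the groups.

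Under Primary and Secondary Outcomes, self-efficacy is in all five questionnaires and is compared between groups at the end of week 3. The Statistical Analysis section compares steps, compliance and fitness by t test, and then adds confounders identified post hoc to regression models.

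**The concern.** A variable used as a starting value or an adjustment covariate should be one that allocation cannot have changed. Here a patient answers the first questionnaire already knowing the group and, in the intervention group, already holding a step tracker and an app linked to a nurse coach. The protocol predicts higher self-efficacy in that group because of the extra guidance and support, and by its own timeline the technology training precedes the first score. Part of the effect may therefore already be in that score.

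Recalled pre-event activity differs in kind. Allocation cannot change what the patient did before the cardiac event, but it can change how the patient reports it. It is the only measure of earlier activity described, because accelerometer steps are specified only for the three study weeks.

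Two uses are exposed. The comparison of trajectories starts from a point that is itself post-randomisation. And if a questionnaire variable looks imbalanced and enters a model post hoc, the imbalance may be treatment effect or reporting rather than chance. Adjusting for it then shifts the estimate. The protocol places randomisation within the meeting so as to protect against nurse bias, but gives patient self-report no such protection, and the Discussion does not list this as a limitation.

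**Working it through.** **1. Order of events.** Preoperative screening; consent before surgery; surgery and 3-5 days in hospital; introduction meeting at discharge (programme explained, then allocation, then devices and app handed over); discharge; first questionnaire by email. The abstract puts the first questionnaire at discharge rather than right after it. This does not alter the order, because the questionnaire is emailed and allocation happens inside the discharge meeting. The text does not say which questionnaire carries the International Physical Activity Questionnaire (IPAQ), but every one described comes after allocation.

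**2. The plan's own figure.** Inputs from Sample Size Calculation: difference 2000 steps, SD 3000, 50 per group, alpha .05 (two-sided assumed). d = 2000/3000 = 0.667. Noncentrality = 0.667 × √(50/2) = 3.33 on 98 df, giving power 0.910. The t-based requirement for 90% is 48.3, so 49 per arm, 98 in total, against 100 stated. The sample size holds and is untouched by this point.

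**3. Illustration for self-efficacy.** None of these inputs is in the protocol: week-3 effect d = 0.5 SD; correlation r between first and week-3 score; allocation shifts the first score by s SD in the direction of the effect.

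- Adjusted (ANCOVA) estimate = d − r·s.
- Standardised for power = (d − r·s)/√(1 − r²), noncentral t, 50 per arm, two-sided .05. The small loss of precision from the group difference in the covariate is ignored.
- Unadjusted: noncentrality 0.5 × 5 = 2.5, power 69.7%, whatever s is.

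With r = 0.6, √(1 − 0.36) = 0.8:

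| s | Adjusted effect | Divided by 0.8 | Power |
|---|---|---|---|
| 0 (clean) | 0.50 | 0.625 | 87% |
| 0.1 | 0.44 | 0.550 | 78% |
| 0.2 | 0.38 | 0.475 | 65% |
| 0.3 | 0.32 | 0.400 | 51% |

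The break-even with no adjustment is where 0.5 − 0.6s = 0.5 × 0.8 = 0.40, so s = 0.10/0.6 = 0.17 SD. Beyond that, adjusting for the late score is worse than not adjusting.

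Other correlations, at s = 0.2: r = 0.3 goes from 74% (clean) to 63%; r = 0.7 from 93% to 70%. Over r = 0.3 to 0.7 and s = 0.1 to 0.3, the adjusted estimate moves by r·s, from 0.3 × 0.1 = 0.03 SD to 0.7 × 0.3 = 0.21 SD. A change from the first score loses all of s: 0.5 falls to 0.4, 0.3 or 0.2.

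**4. Illustration for steps.** If recalled activity were added as a covariate and the same assumed range applied, the adjusted step difference would move by 0.03 × 3000 = 90 to 0.21 × 3000 = 630 steps, against the 2000-step minimum effect of interest. The direction depends on which way allocation colours recall, and the documents give no evidence on that.

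**The case against.** The strongest reply is that no stated main comparison depends on the first questionnaire. Self-efficacy is compared between randomised groups at week 3, with no change score or adjustment stated. Average daily steps are compared first by a t test, which needs no baseline. The power losses above belong to an analysis of covariance that the protocol does not plan, and self-efficacy is not in the list of outcomes for the two-step procedure. The protocol calls only pre-event activity baseline, not the first self-efficacy score. The comparison over the weeks is exploratory, and it can still be interpreted if the first point is not read as an untreated starting value. All of this stands, and it limits the harm to secondary and conditional uses.

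A reader might go further and infer that the trial has no valid covariates for the primary outcome, or that its self-efficacy result is biased by the timing. The documents support neither. Demographic and clinical data come from usual care, and patients have a preoperative workup; allocation cannot alter what was recorded before it. An unadjusted week-3 comparison is the same whenever the first questionnaire was sent. Nor is it certain that adjustment removes part of the effect: that requires the first score to shift towards the week-3 effect, and the size and direction of any shift are unknown.

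The reply does not remove the exposure. The post hoc step leaves open which variables enter the models for steps and fitness, and questionnaire variables are natural candidates. The trajectory comparison is planned. The timeline figure and the appendix of self-report measures are not visible here, but the text fixes the order by itself.

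**Conclusion.** The point holds in a limited form. As scheduled, the first self-efficacy and attitude scores and the recalled pre-event activity are post-randomisation reports from unblinded patients. The unadjusted week-3 self-efficacy comparison, the unadjusted step comparison and the sample size are unaffected by this timing. The comparison of psychological states over the weeks, and any post hoc adjustment for these variables, could absorb part of the treatment effect or carry reporting bias.

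The conclusion about order rests on the text alone. The size rests entirely on assumed values and is an illustration: adjustment would move an estimate by 0.03 to 0.21 SD. With d = 0.5 and r = 0.6, a clean score would raise power from about 70% to 87%, and a late score could give back that gain or more. The change is worth making because it is cheap and a pre-allocation measure cannot be obtained afterwards.

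**What to change.** 1. Have questionnaire 1 (self-efficacy, attitude, IPAQ, trait self-control) completed in the introduction meeting, after the walking programme is explained and before the computerised allocation. The protocol already places allocation "before the tutorials about how to use the (condition-dependent) technologies", so the slot exists. Release the allocation only once the questionnaire is complete.
2. Alternatively, take the IPAQ and trait self-control at consent, since neither depends on the walking programme.
3. Prespecify the pre-allocation self-efficacy score as the covariate for the week-3 self-efficacy comparison, and use it as the starting point of the trajectories.
4. State that variables first measured after allocation will not be used as adjustment covariates in the post hoc regression step.

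**Cost:** about 10 more minutes in a meeting that already takes place, and a small protocol amendment; no extra visit or staff. It needs to be in place before the first patient is enrolled, planned for September 2020. If some patients are enrolled under the present schedule, report their first scores as post-randomisation measures and keep them out of the covariate set.
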